**Fig. 1 Fig1:**
[figure not shown]
Trial flow

**Table 2 Tab2:** Study flow chart

	Study period												
	Pre-Treatment		Treatment									Follow-up	
Week	0		1	2		3	4		5	6		10	18
Visit	Screening	Baseline	V1-V5	V6-V10	V10	V11-V15	V16-V20	V20	V21-V25	V26-V30	V30	V31	V32
Informed consent	X												
Sociodemography	X												
Pregnancy test^1^	X												
Physical/neurological examination	X												
Concomitant treatment^2^	X	X			X			X			X	X	X
SCID-5-PD	X												
ATHF-SF	X												
MADRS (item 10 only)	X												
HDRS-17	X				X			X			X	X	X
Randomization	X												
MADRS (complete)		X			X			X			X	X	X
BDI-II		X			X			X			X	X	X
CGI		X			X			X			X	X	X
WHO-5		X									X	X	X
WPAI		X									X		X
THINC-it^®^ (test of cognition)		X									X		X
CTQ		X											
EHI		X											
MRI^3^		X											
Genetics^3^		X									X		X
Determination of resting motor threshold^4^		X											
Active iTBS/cTBS sham iTBS/cTBS													
Safety check													

^1^Pregnancy test is only necessary for women in child-bearing age; if a blood sample is taken as part of the clinical routine, it is advisable to check a possible pregnancy with a blood test. Otherwise, a urine test can be used to avoid unnecessary risks

^2^Concomitant medication and/or any type of psychotherapy will be documented for each patient for his/her entire participation period

^3^MRI and Genetics are not part of the standard protocol but belong to two satellite projects

^4^Alternatively, the threshold can also be determined directly before the first stimulation, i.e. in visit 1

Study treatment will start on Monday within the week after completion of the baseline session (deviations in case of holidays are possible). During the treatment phase, each patient will receive a total of 30 TBS sessions over a period of 6 consecutive weeks (one session daily from Monday to Friday).

Ratings will take place at the end of the 2nd, 4th, and 6th weeks after the respective stimulation session.

Within the follow-up period two visits are scheduled, 1 month and 3 months after the end of treatment. Patient participation in the study will end with last follow-up.

### Assessment

#### Clinical measures

The tests and questionnaires performed during screening, baseline, visits 10, 20 and 30 and the two follow-up visits are summarized in Table 2. As such, the screening consists of (1) registration of socio-demography (age, sex, years of education), (2) documentation of concomitant treatment (medication and any type of psychotherapy), (3) physical-neurological examination, (4) psychiatric examination including differential diagnosis of MDD according to DSM-5 criteria, the Structured Clinical Interview for DSM-5 Personality Disorders (SCID-5-PD), the Antidepressant Treatment History: Short Form (ATHF-SF), the Hamilton Rating Scale for Depression—17 items (HDRS-17), and item 10 (suicidal thoughts) of Montgomery-Asberg Depression Rating Scale (MADRS) and (5) a pregnancy test if indicated (female patients in child-bearing age).

The baseline will comprise further psychopathological examination, i.e. MADRS (complete version), Clinical Global Impression Scale (CGI), Beck Depression Inventory (BDI-II), Childhood Trauma Questionnaire (CTQ), World Health Organization Five Well-Being Index (WHO-5), and Work Productivity and Activity Impairment Questionnaire (WPAI). In addition, the baseline session also includes the Edinburgh Handedness Inventory (EHI) and the THINC-Integrated Tool (THINC-it^®^), a computerized test battery for measuring cognitive functions in patients with major depression [41].

During the treatment period, visit 10 (end of 2nd week) and visit 20 (end of 4th week) comprise HRSD-17, MADRS, CGI, and BDI-II. Visit 30 (end of treatment) will additionally include WHO-5, WPAI and the repetition of the THINC-it^®^ cognitive test battery. The first follow-up is identical to visits 10 and 20. The second follow-up is identical to visit 30.

Regarding the primary endpoint (MADRS), a comprehensive rater training is delivered comprising training and a validation phase. For the training phase, three videos are available to explain the (expected) ratings of the different items. A fourth video is used to assess, i.e. whether the raters' assessments match the sample solution. Any deviations will be discussed with the principal investigator. If there are deviations of more than ± 1 point, the training must be repeated. Furthermore, instructions for raters will be improved based on these discussions and communicated to all study centers.

#### MRI acquisition

Study participants will undergo MRI prior to the first TBS intervention including acquisition of a magnetization prepared rapid acquisition gradient echo (MPRAGE) sequence to obtain high resolution T1-weighted images (TR = 2.3 s, TE = 4.16 ms, TI = 0.9 s, flip angle 9°, voxel size = 1 × 1 × 1 mm^3^), a sampling perfection with application optimized contrasts using different flip angle Evolutions (SPACE) sequence to obtain high resolution T2-weighted images (TR = 5 s, TE = 383 ms, TI = 1.8 s, voxel size = 1 × 1 × 1 mm^3^), diffusion MRI (TR = 6 s, TE = 55 ms, bandwidth: 1930 Hz/voxel, flip angle = 90°, 70 axial slices, voxel size of 2 × 2 × 2 mm^3^) along 64 independent directions using a b-value of 1500 s/mm^2^, a gradient echo fieldmap for image distortion correction (TR = 0.4 s, TE(1) = 5.19 ms, TE(2) = 7.65 ms, flip angle = 60°, 36 slices with 3 mm slice thickness + 1 mm gap, voxel size = 3 × 3 × 4 mm^3^), and functional MRI (400 images, 69 transversal slices acquired interleaved, TR = 1.5 s, TE = 30 ms, flip angle = 70°, voxel size = 2 × 2 × 2 mm^3^, multiband acceleration factor 3) obtained during resting-state with eyes-open and presentation of the movie paradigm Inscapes [42]. Inscapes is freely available via www.headspacestudios.org/inscapes and features abstract shapes without a narrative or scene-cuts and was designed to decrease head-motion and increase wakefulness while minimizing cognitive load during the acquisition of resting-state functional MRI data.

#### Multi-omics analysis

Participation in the multiomics satellite study involves the collection of a blood sample (30 ml EDTA, 2.5 ml PAXgene™) at three-time points (baseline, end of 6th week, and 2nd follow-up) to allow for genetic, epigenetic, and gene expression analyses. To investigate epigenetic markers potentially predicting therapy response, epigenome-wide analyses will be performed using the Illumina EPIC MethylationEPIC BeadChip array [43]. DNA methylation of top hits will be validated by pyrosequencing. For investigating gene expression markers whole-genome RNA-sequencing will be performed on whole blood samples. Expression levels of differentially expressed key hub and regulator genes will be validated by quantitative RT-PCR (= reverse transcription-polymerase chain reaction) using globin reduced total RNA derived from whole blood. To study the potential influences of genetic variation on epigenetic regulation and phenotypic outcome, genetic analysis of the candidate genes will be conducted.

### Randomization

The Institute of Clinical Epidemiology and Applied Biostatistics of the University of Tübingen (IKEaB) is responsible for randomization. By using the randomization tool of the software nQuery (release 8), patients will be allocated either to the active or placebo group in 1:1 ratio with varying block lengths. Additionally, the order of cTBS and iTBS in the first session (cTBS–iTBS or iTBS–cTBS, respectively) will be randomized and subsequently alternated in all following sessions. Randomization is stratified for the study center.

Technically, the IKEaB will receive a list with patient keys (6-digit numerical codes) provided by the manufacturer of the magnetic stimulator (MagVenture^©^, Farum, Denmark). These patient keys must be entered into the magnetic stimulator to start the stimulation session and determine whether the machine delivers verum or sham stimulation (for details see “Intervention”). Each patient key will be used only once during the entire trial and each randomized patient will keep his/her patient key until the end of treatment. The patient keys are matched to the randomization list obtained from the software nQuery by using the statistical software SPSS. This will be done by an independent statistician not involved in the study.

The study centers will receive only the patient keys together with the information about the order of iTBS and cTBS on demand by using the computerized randomization tool of our database secuTrial^®^. The patient key itself cannot be used to identify the treatment arm, thus ensuring blinding of study physicians, TMS-operators, patients, and data analysing statistician.

### Intervention

#### Determination of stimulation intensity

At the end of baseline/before the first stimulation session, the study physician will determine the individual stimulation intensity based on the resting motor threshold (RMT), which will be measured separately for the right and left primary motor cortex. It is defined as the lowest stimulation intensity that induces a motor response in at least five of ten TMS stimuli. According to the standard clinical practice, it will be assessed by visual observation of contralateral thumb twitches [4]. Individual stimulation intensity will be set to 80% RMT for left iTBS and right cTBS during the 6-week treatment period. Pulse form will be biphasic, with an anterior–posterior to posterior–anterior current direction. The handle of the coil will be oriented backwards rotated about 45° from sagittal orientation with the axis pointing towards the nasion.

#### Determination of targeted brain areas

The target areas for stimulation are the left and right dlPFC. Since neuronavigation is not practicable in such a large sample size, following the EEG 10–20 system is accepted as the most feasible approach to locate the specific brain areas [18, 44, 45]. We will use the beam F3 system to determine the individual stimulation targets F3 and F4 corresponding to the left dlPFC the right dlPFC, respectively. The orientation of the coil handle will be similar to the stimulation of the respective motor hot spot.

#### Stimulation: cTBS and iTBS

Based on the standard TBS protocol [22], each stimulation session will comprise two trains of 600 stimuli (Fig. 2) each applied in bursts of three pulses at 50 Hz given every 200 ms. On the left-side, activity enhancing iTBS (2 s on/8 s off) will be applied 20 times (600 stimuli) for a total duration of 3 min 12 s. In the same session, cTBS targeting the right dlPFC will be applied continuously for 40 s (600 stimuli). For the first session, the order of cTBS/iTBS will be determined by randomization and will alternate in each following session to preclude order effects.

**Fig. 2 Fig2:**
[figure not shown]
Bilateral Theta burst stimulation during TBS-D. Simplified sagittal brain drawing, TMS figure-of-eight coil over the left and right dorsolateral cortex (F3/F4, EEG 10–20 system). The coil is directed to the nasion. Modified picture taken from pixabay.com

#### Technical devices

Both, the determination of the RMT as well as the active and sham TBS will be carried out with the same magnetic stimulator (MagPro X100 or R30; MagVenture^©^, Farum, Denmark). The determination of the RMT will be performed with a 150° angled figure-of-eight coil (Cool B70) and the verum or sham stimulation with the corresponding active-placebo coil (Cool B70 A/P). To activate the treatment stimulation (either verum or sham), the TBS-operator has to enter a six-digit numerical code—the patient key (for details see section “Randomization”)—into the stimulator. Depending on the orientation of the A/P coil, either the message "coil ready" or "turn coil" appears. The orientation of the coil with both sides looking alike determines whether TMS pulses target the brain (real) or the opposite direction (sham). Since in both conditions a “real TMS pulse” is triggered, the acoustic artefact is similar. The manufacturer will train the study staff in the operation of the simulator, and the principal investigator (CP) will train all study personnel operating TBS in determining treatment areas and coil position to ensure a consistent approach regarding stimulation procedure across all trial sites. All centers will also receive a training video.

#### Stimulation: electrical co-stimulation

The magnetic stimulation is accompanied by electrical co-stimulation to compensate for the typical somatosensory artefact and therefore ensure the greatest possible degree of blinding on the patient's side. For this purpose, flat electrodes (2 × 3 cm) will be attached to the patient's forehead: during left-sided iTBS, the center of the first electrode is fixed to FZ (EEG 10–20 system), the second electrode is fixed on the left forehead, i.e. rectangular aligned to the upper edge of the FZ-electrode. The distance between the edges of the two electrodes is 0.5 cm. During right-sided cTBS, the electrodes’ position is analogous with the second electrode on the right forehead, i.e. rectangular aligned to the upper edge of the FZ-electrode. The intensity of the co-stimulation is technically linked with the intensity of TBS. It is applied with 50% of the maximal output and, on this basis, automatically adjusted to the individual stimulation intensity in the active and the sham group.

#### Blinding

The use of the active/placebo coil in combination with the patient keys and electrical co-stimulation allows a double-blind design. As the patient key itself does not allow group assignment and the statistical center (IKEaB) is responsible for central randomization (for details see section “Randomization”), neither the patient, nor any study staff member is aware of group assignment. As an additional precaution, study staff members administering the ratings may not attend the stimulation sessions. Blinding for patients, all study staff members, and the biostatistician responsible for statistical analyses will be maintained until the data analysis is complete.

#### Concomitant treatment

Within the study, no specific antidepressant medication is mandatory. However, if present, the antidepressant therapy must be kept constant, which means that medication at or above the "minimum oral dose"(MOD) specified in the ATHF-SF [46] has to remain unchanged 4 weeks before and 6 weeks during study treatment. Changes below the MOD are considered as uncritical. Changes after the end of treatment are registered in the follow-up sessions. Critical changes during the treatment period lead to exclusion from the per protocol analysis. Antiepileptic drugs and/or benzodiazepines corresponding to > 1 mg lorazepam per day are not allowed during the trial. Accompanying psychotherapy is continued as specified in the individual treatment plan.

### Study endpoints

#### Primary outcome measure

We selected the difference in treatment response-rates (MADRS reduction of at least 50% of baseline value after the end of treatment period) between active combined iTBS/cTBS and the placebo condition as the primary endpoint. Thus, ambiguities regarding the clinical relevance of potentially small mean difference should be avoided and the results will derive a clear statement on the number to treat for a substantial treatment effect.

#### Secondary outcome measures

The considered secondary endpoints are (1) remission rate after treatment period which is defined as MADRS score ≤ 10 (2) comparison (active vs. sham) of raw score reduction of MADRS, HDRS-17, CGI, BDI-II, WHO-5, and WPAI during (a) treatment phase and (b) during follow-up (1 month and 3 months after end of treatment) compared to baseline for each time point; (3) number and severity of adverse events in both treatment arms and (4) deterioration rate after treatment which is defined as an increase of MADRS score of 25% compared to baseline.

### Sample size calculation

In an own pilot study (*n* = 32) we found 9/16 (56%) responders (MADRS ≤ 50% of baseline) in the verum group and 4/16 (25%) responders in the sham group [28]. In a second pilot study (*n* = 60) of another group [29] response rates (HDRS-17 ≤ 50% of baseline) were 66.7% vs. 13.3% after 2 weeks treatment and 4/15 (27%) vs. 1/15 (7%) after week 14. In the third pilot study (*n* = 56) [30] response rates (HDRS-17 ≤ 50% of baseline) were 55% (bilateral TBS) and 30% (sham TBS), 7 weeks after initiation of a 3 weeks treatment. In a recent large (total *n* = 385) clinical trial [18] comparing iTBS (*n* = 193) with 10 Hz rTMS (*n* = 192) the outcome criterion of HDRS-17 ≤ 50% of baseline was achieved by 49% of patients treated with iTBS. Based on these studies, we conservatively assume a response rate of 49% vs. 30% (combined bilateral TBS vs. sham TBS) using the criterion MADRS reduction of at least 50% compared to baseline. This leads to a sample size of 103 subjects per group (Chi-square test, alpha = 0.05 two-sided, beta = 0.2), totally 206 evaluable subjects. As we will recruit in seven centers we increase the sample size by *n* = 6 to compensate for degrees of freedom in a stratified analysis which leads to 212 patients. The analysis will be done on the full set of patients except for those refusing consent during the study or not receiving at least one treatment. We expect a low dropout rate and therefore, we increase the sample size by 24 subjects to adjust for 10% dropouts, which leads to a total n of 236 patients.

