### Statistical analysis

Data of patients who receive at least one treatment will enter the primary intention-to-treat (ITT) analysis. The secondary per-protocol analysis (PP) will consider data of patients who participated in at least 80% (24/30) of the intended stimulation sessions.

Missing values will be imputed using multiple imputation approaches. The multiple imputation approach is used in the primary analysis. Complete case and last observation carried forward analysis will serve as sensitivity analysis. We expect to use monotone data imputation (missings caused by dropouts but not intermediate missing values in the time course) [47]. Thus natural predictors in the imputation model are preceding measurements of the outcome variable including baseline. Additionally, potential predictors as listed in the description of exploratory analyses will be included. Reproducibility will be ensured by the use of random seeds and variation due to the sampling process in the imputation will be reduced by a large number of imputation samples (*n* = 1000). The primary analysis will use a logistic regression model with MADRS ≤ 50% of baseline (yes/no) as dichotomous outcome, treatment arm as factor, baseline MADRS (continuous scale) and study center as covariate (factor). The goodness of fit for the logistic regression analysis will be inspected by use of the Hosmer–Lemeshow test. No interim analysis or planned subgroup analyses will be performed.

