## Discussion

Lack of efficacy, insufficient tolerability or poor acceptance of common therapeutic approaches are major challenges in the treatment of MDD. Against this backdrop and based on comprehensive neurophysiological knowledge, rTMS has been established as an effective treatment option. Multiple clinical trials demonstrated and meta-analyses confirmed [3, 34, 48, 49] its efficacy in treating unipolar depression. However, particularly European treatment guidelines do not yet provide a clear recommendation for the application of rTMS [17]. Thus, clinicians are still hesitant in offering rTMS as a routine treatment option in MDD. Not the least, common rTMS treatment protocols are rather time-consuming and costly. With TBS, a substantially briefer and most likely at least similar effective [18, 28, 29] form of rTMS is available. However, although the recently documented non-inferiority of TBS compared to standard 10 Hz rTMS [18] is very valuable, it does not yet address the persisting doubts about the efficacy of rTMS in MDD treatment.

To meet that need, we designed this study (TBS-D) as a multicenter randomized placebo-controlled clinical trial to provide lacking evidence for a decisive recommendation regarding the use of rTMS in MDD treatment and to prove that 6 weeks of bilateral TBS—a particularly efficient and tolerable form of rTMS—is an effective add-on to standard MDD therapy. A positive result would primarily promote the adoption of rTMS for MDD treatment in general. Secondly, proof of the effectiveness of TBS would establish this faster and less burdening form of treatment. Thirdly, positive results would allow for more intensive treatment regimens like accelerated TBS [50] and thus path the way to a personalized treatment approach [20]. Regarding dropouts, we are confident to minimize them in particular because, the TMS operator sees the patient on a daily, the rater on a weekly basis. Hence, a strong bond between the study team and patient is established and the continuation of treatment is ensured. In addition, the well-known and robust placebo effect of TMS treatment should prevent dropouts in both treatment arms. However, for statistical analysis, we are aware of the risk of informative dropouts, depending on study arm or treatment success. A thorough analysis of patients who dropped out compared to patients with complete follow-up will be performed. The use of multiple imputations hopefully will adjust for this possible drawback.

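### The protocol gives two different rules for treated patients who withdraw consent: one removes them from the primary analysis, the other keeps and imputes them

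*Protocol article*

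**What the plan says.** Two sections of the protocol article state who enters the analysis.

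- **Sample size calculation:** the analysis uses the full set of patients "except for those refusing consent during the study or not receiving at least one treatment".
- **Statistical analysis:** "Data of patients who receive at least one treatment will enter the primary intention-to-treat (ITT) analysis". No exception for withdrawn consent is given. On missing values, "The multiple imputation approach is used in the primary analysis", and the missingness that is foreseen is "missings caused by dropouts but not intermediate missing values in the time course".

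The primary endpoint is response, defined as "MADRS reduction of at least 50% of baseline value after the end of treatment period". Table 2 schedules complete MADRS ratings at baseline, at the end of weeks 2, 4 and 6, and at two follow-up visits.

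On dropout, the Discussion says "we are aware of the risk of informative dropouts, depending on study arm or treatment success". It announces a comparison of dropouts with completers and expresses the hope that multiple imputation will deal with the problem.

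The section on documentation, monitoring and data management leaves the assignment of patients to analysis populations to a blind data review, without saying which of the two rules that review should apply.

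**The concern.** The two rules agree on patients who were never treated: both leave them out. They disagree on patients who received at least one session and then withdrew consent. The sample size section lists refusal of consent separately from non-receipt of treatment and places it during the study, so as worded it reaches treated patients.

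Three things are at stake if that rule is followed:

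- MADRS ratings already taken at weeks 2 and 4 would be thrown away, although the analysis section names preceding measurements of the outcome as the natural predictors in the imputation model.
- Multiple imputation, the remedy on which the Discussion relies against informative dropout, cannot act on patients who are no longer in the set.
- If patients who withdraw differ in outcome from those who stay, the observed response rate of their arm shifts. Depending on which arm loses more of them, the difference between arms can grow or shrink.

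Membership of the primary set of a confirmatory trial needs one answer before unblinding. Here the text supplies two.

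**Working it through.** **1. The plan's own figure.** The inputs come from the sample size section: response rates of 49% and 30%, chi-square test, two-sided alpha 0.05, power 80%. With pooled variance and no continuity correction, and a mean rate of 0.395:

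n per arm = [1.960 × √(2 × 0.395 × 0.605) + 0.842 × √(0.49 × 0.51 + 0.30 × 0.70)]² / 0.19² = (1.355 + 0.571)² / 0.0361 ≈ 102.7, rounded up to 103.

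Then 206 + 6 = 212, and 212 / 0.90 = 235.6, rounded up to 236. The stated sample size is reproduced. It does not depend on which rule for withdrawn consent is adopted.

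**2. The two rules side by side.**

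| Patient | Sample size section | Statistical analysis section |
|---|---|---|
| Randomised, never treated | out | out |
| Treated, drops out without withdrawing consent | in | in, imputed |
| Treated, withdraws consent | out | in, imputed |

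Only the last row conflicts.

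**3. What deletion could do.** The documents give no rate of consent withdrawal, so everything here is assumed. Take 236 / 2 = 118 per arm and k treated withdrawers in one arm, all of whom would have been non-responders. After deletion, a true rate p becomes p × 118 / (118 − k).

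No true effect, both arms at 30%, deletion in one arm only (rejection rates by normal approximation):

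- k = 12: 35.4 / 106 = 33.4%, a shift of 3.4 points; two-sided rejection rate about 8.5%.
- k = 6: 35.4 / 112 = 31.6%, a shift of 1.6 points; rejection rate about 5.8%.
- k = 12 in each arm: both rates become 33.4%, the difference is 0 and the rejection rate stays at 5.0%.

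Assumed effect, 49% against 30% (true difference 19.0 points):

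- k = 12 in the sham arm only: 49.0 − 33.4 = 15.6 points.
- k = 12 in the active arm only: 57.82 / 106 = 54.5%, and 54.5 − 30.0 = 24.5 points.
- k = 12 in each arm: (57.82 − 35.4) / 106 = 21.2 points. With a true effect, equal withdrawal can still change the estimate.

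If withdrawers respond at the same rate as the rest of their arm, the shift is 0 in every case.

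**4. What imputation would recover.** The shifts in step 3 are measured against the true outcomes, not against the imputed analysis. Take again 30% in both arms and 12 active-arm non-responders who withdraw, now with no rating after baseline.

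- Imputed at the active completers' rate of 33.4%: (35.4 + 12 × 0.334) / 118 = 33.4%. The shift is still 3.4 points.
- Imputed at the pooled completers' rate of (35.4 + 35.4) / (106 + 118) = 31.6%: (35.4 + 12 × 0.316) / 118 = 33.2%. The shift is 3.2 points.

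With no early ratings, imputation and deletion give almost the same answer. Imputation gains on deletion to the extent that week 2 and week 4 ratings exist and predict the final score; the documents do not allow that gain to be quantified.

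**The case against.** The strongest reply is that the statistical analysis section is the formal definition and the other sentence is an aside between two sample size adjustments. Refusing consent may also mean withdrawing permission to use data, in which case the sentence only names patients who cannot lawfully be analysed. Both points narrow the issue without removing it. The aside states how the analysis will be done, no text ranks the two sections, and the term is not defined.

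A reader might infer more than the protocol supports, in four ways:

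- **That the comparison would be biased.** Bias needs withdrawal to be related to outcome. Inflation of the type I error needs it also to differ by arm.
- **That the protocol expects informative dropout.** The Discussion speaks of awareness of a risk, of confidence that dropout can be kept low, and of dropout in general rather than withdrawal of consent.
- **That 3.4 points, or an error of about 8.5%, is the cost of choosing one rule over the other.** Those figures compare deletion with known outcomes. Without early ratings, imputation gives nearly the same shift.
- **That the primary set must contain all randomised patients.** The conflict does not require this, since both sections already agree on at least one treatment.

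**Conclusion.** The contradiction stands, confined to treated patients who withdraw consent during the study. The protocol excludes them in one section, includes and imputes them in another, and leaves the blind data review without a rule. Following the exclusion would discard collected ratings and bypass the protocol's own safeguard against informative dropout. It could therefore bias the response-rate comparison in either direction.

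The size is unknown because no consent-withdrawal rate is stated. The figure of about 3.4 points is an extreme case: 12 of 118 patients, all non-responders, all in one arm, at a true rate of 30%, set against their true outcomes. Imputation would remove only part of that shift, depending on the early ratings available. The type I error stays at 5% with equal withdrawal in both arms under the same assumptions, and there is no bias if withdrawers respond like the rest of their arm.

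**What to change.** Align the sentence in the sample size section with the statistical analysis section, so that both state one primary set:

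- all randomised patients who received at least one session are included;
- for those who withdraw consent, data collected up to withdrawal are used and later values are multiply imputed;
- only patients who forbid the use of data already collected are removed, and their number is reported by arm.

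This also settles what refusing consent means and gives the blind data review a rule to apply. The cost is one sentence. No patients are added, and 103 per arm, 212 and 236 stay as they are.
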